## Abstract

**Background:**

A thoracolumbar fracture is the most common fracture of the spinal column. Where the fracture is not obviously stable or unstable, the optimal management is uncertain. There are variations between surgeons, treating centres and within the evidence base as to whether surgical or non-surgical approaches should be used. In addition, the boundaries of this zone of uncertainty for stability are unclear.

This study has been designed in response to an NIHR HTA commissioning brief to assess the feasibility of undertaking a large-scale trial to evaluate the effectiveness of surgical and non-surgical treatments for thoracolumbar fractures without neurological deficit.

**Methods:**

Assessment of feasibility will be addressed through three elements: a randomised external feasibility study, a national survey of surgeons and a qualitative study.

The external feasibility study is a pragmatic, parallel-group, randomised controlled trial comparing surgical fixation (intervention) versus non-surgical management (control). Recruitment will take place in three secondary care centres in the UK.

The primary outcome is recruitment rate, defined as the proportion of eligible participants who are randomised. Further outcomes related to recruitment, randomisation, drop-out, cross-over, loss to follow-up, completeness of outcome data, study processes and details of the interventions delivered will be collected.

The survey of surgeons and qualitative study of clinicians, recruiting staff and patients will enhance the feasibility study, enabling a broad overview of current practice in the field in addition to perceived facilitators and barriers to running a full-scale trial.

**Discussion:**

PRESTO is a feasibility study which aims to inform methodology for a definitive trial comparing surgical fixation with non-surgical management for patients with stable thoracolumbar fractures.

**Trial registration:**

The trial is registered with the International Standard Randomised Controlled Trial Register (ISRCTN12094890). Date of registration was 22/02/2018 (http://www.isrctn.com/ISRCTN12094890).

## Background

Thoracolumbar fractures are the most common fracture of the spinal column [1]. The potential consequences for people who experience a thoracolumbar fracture include pain, loss of function impacting on the ability to work and undertake other activities, spinal deformity (kyphosis), and in some cases, paralysis.

There appears to be informal consensus that simple compression fractures without neurological complications can be managed without surgery [2], and this is reflected in UK practice. Similarly, obviously unstable fractures where there is neurological damage or an elevated risk of damage will require surgical fixation. However, there is a zone where there is variation between surgeons and between centres as to whether surgical or non-surgical approaches should be used. In addition, there is uncertainty in the evidence base as to the most effective treatment in terms of pain, speed of recovery, return to normal activities, prevention of kyphosis, and any associated problems with chronic back-pain and balance. The boundaries of this zone of uncertainty are unclear.

The funder commissioning brief requested inclusion of patients with high and low energy fractures. Although there are differences between the populations, in the context of a pragmatic trial, and with the implementation of stratified randomisation (high-energy trauma fractures and osteoporotic fractures) and appropriate analysis, it may be possible to include both groups in the same trial. Equally, there is likely to be differences in opinion amongst spinal surgeons regarding the acceptability of such a trial. Therefore, testing this in a feasibility study is important and we propose to include high-energy trauma and low-energy osteoporotic fractures.

A Cochrane review [3], evaluating the evidence on the effectiveness of surgical and non-surgical treatments for thoracolumbar burst fractures without neurological deficit, concluded that there is a need for a large, multicentre, high-quality and adequately reported randomised controlled trials (RCT) of such interventions to address the evidence gap for these types of fractures. This study, designed in response to a NIHR HTA commissioning brief, will assess the feasibility of undertaking such a large-scale randomised clinical trial.

## Aims and objectives

The aim of this study is to establish whether it is feasible to deliver a trial comparing surgical fixation to initial non-surgical management for patients with a stable thoracolumbar fracture without spinal cord injury.

The study will address the following specific questions:
Are surgeons willing to randomise eligible patients and adhere to the allocation to (i) surgical fixation or (ii) initial non-surgical management?Are patients willing to be randomised and adhere to the allocation in a trial comparing the two treatments?What is the completeness of follow-up in this population?Are there a sufficient number of centres and surgeons (with sufficient caseloads of eligible patients) willing to participate in a future RCT to make the trial feasible within a viable timescale?What methods of establishing spinal stability and suitability for surgery or non-surgical management are currently used?What methods of surgical fixation and non-surgical management are currently being used?What are the barriers to successful delivery of a future trial and how can they be overcome?Can the British Spine Registry be used to collect participant data in a trial?What is the most suitable primary endpoint for a main trial?How can we accurately identify, quantify and value economic data to capture the impact of the two treatments on the NHS and productivity?

## Design

The trial objectives will be addressed through three elements:
i.a randomised external feasibility trialii.a national survey of orthopaedic spine surgeonsiii.a qualitative study including clinicians, recruiting staff and patients

## Methods: Feasibility Trial

### Setting

Participants that fulfil trial inclusion criteria will be enrolled from participating secondary care centres. Three participating centres from different geographical regions have been chosen to enhance generalisability and applicability across the UK. Table 1 lists the hospital sites that will be set up to recruit patients into the randomised feasibility trial.

**Table 1 Tab1:** PRESTO participating hospital trust sites

	Study sites
1.	Bart’s Health NHS Trust
2.	Leeds Teaching Hospitals NHS Trust
3.	Cardiff and Vale University Health Board

### Study participants

Patients are eligible to participate in this study if they:
Are aged 16 years or older;Have a diagnosis of a high- or low-energy impact thoracolumbar vertebral body fracture, between T10 and L2, and confirmed by radiograph, computed tomography (CT) scan or magnetic resonance imaging (MRI) with at least ONE of the following criteria:
A kyphotic angle greater than 20° on standing radiographs, or if lying CT or radiograph then 15° of kyphosis; orReduction of vertebral body height by 25%; orFracture line propagating through the posterior wall of vertebra; orTwo contiguous vertebrae involved; orInjury to the posterior longitudinal ligament (PLL) or annulus in addition to the body fracture

Patients will be excluded from this study if they:
Have an unstable fracture which obviously needs surgical stabilisation—decision made by the treating surgeon;Have a spinal cord injury;Have a pathological (other than osteoporotic) fracture, e.g. tumour/infection;Are not considered suitable for surgery.

### Trial interventions

#### Non-surgical management (control) group

Non-surgical management in the control arm will consist of mobilisation in a brace or mobilisation without a brace, as recommended by the treating surgeon in consultation with the participant. The use and discontinuation of the brace is usually decided by the presence or absence of pain at the fracture site on mobilisation, but may also be for a predetermined prescribed period of time. The brace can be any orthotic device which supports the spine above and below the level of the fracture as considered appropriate by the treating surgeon, such as a thoracolumbar sacral orthosis (TLSO).

#### Surgical fixation (intervention) group

Currently in the UK, surgical treatment generally involves either open spinal surgery or minimally invasive surgery and both methods will be acceptable for use in the trial. Both procedures include placement of pedicle screws, but through different surgical approaches.

##### Open pedicle screw fixation

A midline approach is most commonly performed. Blood loss is minimised with diathermy dissection including careful haemostasis using bipolar and haemostatic agents. The junction between the pars interarticularis, lateral hemifacet and transverse process is identified and a starter awl, then pedicle finder is negotiated. A pedicle screw is placed within the pedicle, not too medial (potentially encroaching the spinal canal) or too lateral (potentially breaching the lateral wall and reducing the screw pullout strength). This confirmation is undertaken by direct palpation using a feeler and further confirmation can be achieved with intra-operative fluoroscopic imaging. Following screw placement, rods are locked into the screw heads stabilising the motion segment. Screws are placed in the un-fractured vertebrae either side of the fractured ones.

The surgeon may then decide to perform a spinal fusion by decorticating the bony surfaces and placing local bone graft and use bone substitutes as graft extenders. If surgical stabilisation alone is performed, decortication and graft placement is not undertaken.

##### Percutaneous pedicle screw fixation (minimally invasive surgery)

This follows the same principles. However, it is performed via multiple stab incisions on either side of the midline and is guided by intra-operative fluoroscopy. The advantages of percutaneous fixation are reduced blood loss and slightly reduced surgical time. Only surgical stabilisation can be undertaken with this technique and not spinal fusion.

Otherwise, the protocol follows that of the control group.

#### Rehabilitation

For both the surgical and non-surgical groups, patients will receive physiotherapy as per routine care. Details such as number of sessions and advice given by the physiotherapist will be recorded.

#### Imaging assessments

The routine imaging performed on admission will be used to confirm eligibility.

For the purposes of this trial, no imaging over and above usual care at a participating site will be requested. Information on the imaging undertaken for trial participants will be recorded.

### Primary outcome

The primary outcome will be recruitment rate, defined as the proportion of eligible participants who are randomised.

### Secondary outcomes

In order to investigate feasibility, we will collect data on the following:
(i)RecruitmentNumber of eligible patients;Proportion of eligible patients approached for consent;Proportion of eligible patients not approached for consent and reasons why;Proportion of patients approached who provide consent;Proportion of patients approached who do not provide consent and reasons why(ii)RandomisationProportion of patients providing consent who are randomised;Proportion of patients randomised who do not receive the randomly allocated treatment and reasons why(iii)Cross-overProportion of patients randomised to the non-surgical treatment who receive surgical management, at what time point and reasons why(iv)Drop-outProportion of patients dropping out between randomisation and follow-up at each time-point and reasons why(v)Ability to collect clinical outcome measuresFeasibility of gathering patient reported outcome measures and other outcome measures at baseline and follow-up (proportion of complete data for each outcome measure; proportion successfully gathered through the British Spine Registry)Feasibility of gathering data on complications and adverse events (proportion of complete data)

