#### Complications and adverse events

Information on all complications, additional surgery and adverse events will be collected in line with a study-specific standard operating procedure. Expected complications that will be recorded will include (but not be limited to) the following: death within 30 days of procedure, neurological complications, deep wound infection, superficial infection, rehospitalisation, implant failure, screw pull-out, re-operation and skin problems.

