### Economic evaluation

A full cost-effectiveness analysis will not be undertaken as part of this feasibility study. The economic evaluation will be used to identify data needed for an economic analysis as part of a full-scale trial. Individual participant data from the trial will be used to evaluate resource use, costs, and health outcomes associated with the interventions.

The acceptability of resource use questionnaires to capture the impact of care on the NHS and productivity will be assessed. The costing approach will be conducted from the National Health Services (NHS) and Personal Social Service (PSS) perspective. Health service resource use will be collected prospectively during the study using self-reported questionnaires and hospital forms at 3 and 6 months. Costs components will comprise all initial and subsequent inpatient episodes, outpatient hospital visits and A&E hospital admissions, and primary care visits (e.g. GP, nurse and physiotherapy). The total resource use will be calculated for each participant in both groups for the duration of the study. Health care resource use will be presented for both arms in terms of mean value, standard deviation, and mean difference (with 95% CI) between the groups. Unit costs will be derived from established national costing sources such as NHS reference costs [18], PSSRU unit costs of health and social care [19], and the British National Formulary [20].

The utility of participants will be measured using the EQ-5D-5L at baseline, 3 and 6 months. The raw EQ-5D -5L scores according to domain will be displayed, in order to examine the movements between levels for each domain according to the trial arm. Utility values will be estimated using the mapping function [21] according to the recent NICE statement on the use of the EQ-5D-5L [22].

The nature and amount of missing economic data will be explored which in turn will guide (i) on the sources to be used for the primary and secondary analyses in a full study, and (ii) on the imputation approach for the definitive trial.

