### Adverse event management

All adverse events (AE) requiring reporting (as defined by a study AE reporting procedure) will be reported on an AE form.

Non-serious, expected complications considered to be as a consequence of the surgery or conservative management, such as pain, and reported as complications on the designated forms will not be reported as adverse events in the context of this study.

Serious adverse events (SAEs) will only be reported if they appear to be related to an aspect of taking part in the study. Those events that are confirmed to be related to the research and are unexpected serious adverse events will be reported to the Research Ethics Committee (REC) within 15 days of the Chief Investigator becoming aware of the event.

The research nurse/physiotherapist will record all directly observed AEs and all AEs reported by the trial patient up to 3 months (and up to 6 months for those patients that reach this time point) following their trial treatment.

In addition, sites will be instructed to follow their own local procedures for the reporting of any adverse events linked to clinical care.

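### Completeness of forms, the only stated measure of whether complications and adverse events can be gathered, cannot show how many events were missed

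*Protocol article*

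**What the plan says.** In the Protocol article, *Secondary outcomes*, item (v) names the measure: "Feasibility of gathering data on complications and adverse events (proportion of complete data". No denominator is stated. The item before it applies the same kind of measure to patient-reported and other outcome measures. *Statistical analysis of feasibility trial* lists the proportions to be reported and adds nothing on complication or adverse event data.

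*Complications and adverse events* says "Information on all complications, additional surgery and adverse events will be collected in line with a study-specific standard operating procedure". It then lists expected complications, rehospitalisation and re-operation among them.

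*Adverse event management* describes how events come to notice. Adverse events that require reporting "will be reported on an AE form". The research nurse or physiotherapist "will record all directly observed AEs and all AEs reported by the trial patient up to 3 months", extended to 6 months for patients who get that far. Non-serious expected complications "reported as complications on the designated forms will not be reported as adverse events in the context of this study". For serious events, "Serious adverse events (SAEs) will only be reported if they appear to be related to an aspect of taking part in the study".

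Table 2 schedules contacts at week 2, month 3 and, for some patients, month 6. It has a row for treatment information but none for complications or adverse events.

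*Economic evaluation* provides a second source: "Health service resource use will be collected prospectively during the study using self-reported questionnaires and hospital forms at 3 and 6 months". The cost components include the initial and all later inpatient episodes.

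**The concern.** Completeness suits a questionnaire, because the schedule fixes how many are due and a missing one is visible. Adverse events have no known expected count. On the route described, an event that staff do not observe and the patient does not mention produces no record, and so looks the same as no event.

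The measure therefore answers whether the paperwork is filled in. The feasibility question is also whether events are found. The study exists to settle methods for a definitive trial, and ability to gather complications is one of its listed outcomes. A good completeness figure could be read as evidence that ascertainment works when it carries no information on that point. The gap matters most for later admissions and further surgery, which site staff may not be placed to observe.

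**Working it through.** **The plan's own figures.** The article gives no figure for this measure. Its one design calculation reproduces: 1.96 × √(0.5 × 0.5 / 120) = 0.0895, or ±9%, and 120 × 0.5 = 60. Only the 60 is used below.

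**Symbols.** N is the true number of events, c the share of them recorded, f the share of submitted event forms that are complete, and r the share of scheduled forms completed. All values of c, f and r below are assumptions; the documents give none.

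**Denominator 1: submitted event forms.**
- Measure = (N × c × f) / (N × c) = f.
- Events captured and fully documented = (N × c × f) / N = c × f.

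| c | Measure, f = 0.98 | Captured | Measure, f = 0.90 | Captured |
|---|---|---|---|---|
| 1.00 | 98% | 98% | 90% | 90% |
| 0.75 | 98% | 73.5% | 90% | 67.5% |
| 0.50 | 98% | 49% | 90% | 45% |
| 0.25 | 98% | 24.5% | 90% | 22.5% |

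The measure does not involve c. Its level is f, whatever f turns out to be.

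**Denominator 2: scheduled forms due.** At the target of 60 patients, with about two thirds followed to month 6, forms due = 60 + 60 + 40 = 160.
- Measure = r. With r = 0.95, 0.80 or 0.60, that is 152, 128 or 96 forms, the measure reads 95%, 80% or 60%. Missing forms do lower it.
- Let c now be the share of events recorded on completed forms, and assume events are spread evenly over returned and unreturned forms. Captured = r × c. At c = 0.5 this is 47.5%, 40% or 30%, while the measure still reads 95%, 80% or 60%.

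This denominator is better, but it too is blind to an event missed on a completed form.

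**What a second source adds.** Let A be the rehospitalisations and re-operations on the complication or adverse event forms, and B those found among later inpatient episodes in the resource-use data. The check is A / (A or B). It falls when B holds events that A lacks, which neither completeness figure can do. Events missed by both sources stay invisible, so if no entry is false the result is at or above true capture.

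**Precision.** With an assumed 12 events and half of them on the forms, the approximate 95% half-width is 1.96 × √(0.5 × 0.5 / 12) = 0.28. Fewer events would widen it. *Trial status* reports 11 patients randomised by February 2019, so a small count is likely.

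**The case against.** The strongest reply is that the denominator is simply not stated. The article condenses a fuller protocol and refers to a study-specific operating procedure, an adverse event reporting procedure and a detailed analysis plan, none of them shown. Any of these may define completeness per visit due. That stands: an unstated denominator is not by itself a fault here.

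It is also fair that event-triggered recording is shown only for adverse events. Complications go on separate forms, and the pre-listed items would suit a checklist completed for every patient at scheduled contacts. The missing row in Table 2 settles little, since length of stay and return to work are collected without rows of their own.

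A reader might infer that the measure will read near 100%, or overstate capture by some definite number of points. The documents do not support either. They give no field completeness, form return or event count; at 90% field completeness the measure reads 90%. Nor can one say that it could never show failure: on a scheduled-form denominator, missing forms pull it down.

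A further objection is that resource-use data and safety reports cover different things, because serious events are reported only if related to taking part. This is largely met by limiting the check to rehospitalisation and re-operation. Both are listed as complications to be recorded, so the relatedness filter need not apply. Imprecision from small numbers remains.

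What the reply does not remove is that neither denominator registers an event missed on a completed form.

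**Conclusion.** The point holds in a limited form. Completeness is the only stated measure of whether complications and adverse events can be gathered. It reflects completion of forms or fields and cannot show how many events were missed, whichever denominator is used. This follows from the recording route in *Adverse event management* and needs no assumed numbers; the percentages above only illustrate it. The actual level of the measure and the actual share of events missed are both unknown. Whether complication forms are scheduled or event-triggered is not stated in the article.

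This concerns one descriptive secondary outcome in a study without formal testing. The recruitment rate, its confidence interval and the sample size are untouched. It is a cheap improvement.

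**What to change.** 1. Keep completeness, and define it per patient-visit due: week 2, month 3, and month 6 where due. Count a visit as complete only if complication and adverse event status is recorded, with none entered explicitly.
2. Add a descriptive capture check for rehospitalisation and re-operation only. Take every such event found either on the complication or adverse event forms or among the inpatient episodes after the initial admission in the 3- and 6-month resource-use data, excluding planned admissions. Report the number and proportion that appear on the complication or adverse event forms, and how many patients supplied resource-use data.
3. Say in the report that events missed by both sources cannot be seen.

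The cost is a status item on the visit form if it is not already there, and a small cross-tabulation of data already planned, which can be done at the single end-of-trial analysis. The downsides are few events, hence wide uncertainty, and possibly a less favourable figure than completeness alone would give.
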